Compounding the prevalent biological factors, structural factors further facilitate HIV transmission amongst AGYW [12–14]. Many AGYW, enter into sexual relationships with older partners as a result of socioeconomic deprivation [15], with age-disparate relationships found to increase HIV-acquisition amongst AGYW [16–19]. Age disparate relationships increase AGYW’s susceptibility to HIV acquisition, because older men are more likely to be HIV positive [8, 20, 21], whilst these partnerships are also characterised by inconsistent condom use [22–24] and concurrent sexual partnering [25]. Relationships are also more likely to be transactional in nature [26], which has been demonstrated to also increase HIV acquisition [27]. In addition, AGYW are vulnerable to intimate partner violence (IPV) and dominant male partner behaviours, both of which increase their susceptibility to acquiring HIV [28].

In response to the high and sustained HIV-incidence among AGYW, interventions have been developed and implemented targeting this particular population cohort. The Determined, Resilient, Empowered, AIDS-free, Mentored and Safe (DREAMS) initiative is a comprehensive, multi-sectoral strategy introduced by the United States of America (U.S.) President’s Emergency Plan for AIDS Relief (PEPFAR) in 2014. DREAMS initiatives exist in 10 countries in sub-Saharan Africa: Kenya, Lesotho, Malawi, Mozambique, South Africa, Swaziland, Tanzania, Uganda, Zambia, and Zimbabwe. The initiative consists of evidence-based interventions, aimed at addressing the structural and behavioural drivers that increase AGYW risk of acquiring HIV, including poverty, gender inequality, gender-based violence (GBV), absence of parental and community support, and lack of education and vocational training [29]. The target of the DREAMS initiative is to reduce HIV incidence by 25% amongst AGYW in targeted high-prevalence areas by the end of the first year of implementation and by 40% at the end of the second year of implementation [30].

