### Study objectives

The primary objective of this study is:
Measure the change in HIV-1 incidence following implementation of the DREAMS suite of interventions within a ‘real world, non-trial setting’.

The secondary objectives are to:
Measure HIV prevalence, and proportion of HIV positive AGYW on ART and ART naïve with detectable and undetectable HIV-1 Ribonucleic Acid (RNA) viral load.Measure prevalence of pregnancies and sexually transmitted infections (STIs) including Hepatitis B virus (HBV), Herpes simplex virus type 2 (HSV-2), syphilis, human papillomavirus (HPV*), Chlamydia trachomatis*, *Neisseriae gonorrhoea*, *Trichomonas vaginalis* and *Mycloplasma genitalium.*Measure risky sexual behaviour, specifically, the number of past year sexual partners, condom use, and age-disparate and concurrent partnering.Measure the prevalence of intimate partner violence.Measure performance on selected academic milestones (e.g. academic progress, school completion rates).Measure the economic empowerment of AGYW, socio-economic status of their family and selected parent/guardian/caregiver indicators.To measure the exposure to the DREAMS programme including condom promotion and provision (male and female); HIV testing services (HTS) and linkage to care; GBV prevention and post violence care and support; comprehensive sexual reproductive health rights (SRHR) services; social asset building interventions; school-based HIV and violence prevention; community mobilization and norms change; parenting/caregiver programmes.

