**Measure risky sexual behaviour (e.g. number of [concurrent, lifetime, age-disparate] sexual partners, condom use, age of sexual debut), gender norms, intimate partner violence (including gender-based violence), and selected academic performance indicators (e.g. academic progress, school completion, assertive behaviour, participation in school and sport)**: The prevalence of risky sexual behaviour, gender norms and episodes of intimate partner violence (IPV) within the past year will be calculated with 95% CIs. IPV is assessed using behaviourally specific items developed by the World Health Organisation, and modified and used extensively in South Africa [47]. Five items ask about past experiences of physical violence from an intimate partner, whilst three items ask about sexual IPV in the previous year. Responses to each item are “never”, “once”, or “more than once”. A positive answer to any of the items leads to a woman being classified as having experienced IPV. Only women reporting having a boyfriend, husband, or having had sex with a man are asked these questions. Gender norms are measured using the gender equitable men (GEM) scale, this scale consists of 6 items relating to norms about male-female relationships and interactions. The scale asks respondents how much control their partners have over them in their relationships in relation to the clothes they wear, decisions made in the relationship and who they can spend time with outside of their relationship. Responses to each item are based on a Likert-type scale with responses ranging from strongly agree to strongly disagree. The scale items will be summed and a mean score calculated. Secondary analysis will be disaggregated by age, HIV and STI status and other socio-economic and academic indicators and exposure to DREAMS interventions.

**To measure the impact of economic empowerment, socio-economic status of their family, and selected parent/guardian/caregiver indicators have had on both the HIV incidence among AGYW and prevalence of GBV/IPV perpetrated against AGYW**: Composite scores will be created for AGYW using multiple correspondence analyses (MCA), taking the survey design and sampling weights into account.

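### The past-year IPV outcome is defined from eight items, five of which, as described, have no one-year limit

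*Protocol article*

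**What the plan says.** All the relevant text is in the Protocol article.

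- **Objective.** The secondary objective under Study objectives is "Measure the prevalence of intimate partner violence". It gives no time window.
- **Outcome.** Analysis of secondary objectives supplies the window: "episodes of intimate partner violence (IPV) within the past year will be calculated with 95% CIs".
- **Items.** The same paragraph sets the two groups of items against each other: "Five items ask about past experiences of physical violence from an intimate partner, whilst three items ask about sexual IPV in the previous year".
- **Answers.** "Responses to each item are “never”, “once”, or “more than once".
- **Case rule.** "A positive answer to any of the items leads to a woman being classified as having experienced IPV".
- **Use.** The paragraph goes on to break the results down by age and by DREAMS exposure, among other factors. The next paragraph takes violence against AGYW as an outcome when it looks at economic empowerment and caregiver indicators.

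**The concern.** The window of the outcome and the window of most of the items do not match. As described, a woman of 24 who was hit by a partner at 17, and has met no violence since, answers one physical item positively and becomes an IPV case. If that case definition feeds the prevalence labelled past-year, she is counted in a year in which nothing happened to her.

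Three things are at stake:

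- **Level.** A prevalence labelled past-year would mix ever physical with past-year sexual violence.
- **Age pattern.** Older participants have had more years in which a physical event could occur, so part of any rise with age could be accumulation and not current risk.
- **Relation to DREAMS.** Prevention of gender-based violence is one of the programme's components. Events older than the programme cannot have been prevented by it, yet they would enter the comparison by exposure.

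**Working it through.** **What can be checked.** The article states no IPV prevalence and no precision or power for this outcome, so there is no figure to reproduce. The check is one of logic, followed by an illustration on assumed inputs.

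**Step 1: direction.** Let S be past-year sexual IPV, P past-year physical IPV and E ever physical IPV. Every woman in P is also in E. Therefore

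Pr(S or E) ≥ Pr(S or P).

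The left side is what the case rule measures if the physical items are open-ended; the right side is what the label promises. The inequality is strict as soon as one woman has only older physical violence and no past-year sexual IPV. The answer categories give a count and no date, so older events cannot be removed at analysis.

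**Step 2: possible size.** Write s and p for the past-year prevalences of sexual and physical IPV, and m for the ratio of ever to past-year physical IPV. None of the three is in the article; all are assumptions. With independence of the two types of violence:

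- true past-year prevalence = 1 − (1 − s)(1 − p)
- prevalence under the rule = 1 − (1 − s)(1 − m·p)

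| s | p | m | True past-year | Under the rule | Ratio |
|---|---|---|---|---|---|
| 5% | 10% | 1 | 14.5% | 14.5% | 1.00 |
| 5% | 10% | 1.5 | 14.5% | 19.25% | 1.33 |
| 5% | 10% | 2 | 14.5% | 24.0% | 1.66 |
| 5% | 10% | 3 | 14.5% | 33.5% | 2.31 |

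For the third row: 1 − 0.95 × 0.90 = 0.145; 1 − 0.95 × 0.80 = 0.240; 0.240 / 0.145 = 1.66.

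Over s = 3–10%, p = 5–15% and m = 1.5–3 the ratio runs from 1.16 (s = 10%, p = 5%, m = 1.5) to 2.66 (s = 3%, p = 15%, m = 3). Independence matters. If the rarer type always occurs within the commoner one, each prevalence is simply the larger component, and the ratio over the same inputs runs from 1.0 to 3.0.

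**Step 3: dilution of a change.** Suppose both past-year components fall by 30% and older physical violence stays as it is. With s = 5%, p = 10%, m = 2:

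- one-year window: 14.5% falls to 1 − 0.965 × 0.93 = 10.3%, a fall of 29%
- rule as written: 24.0% falls to 1 − 0.965 × (1 − 0.07 − 0.10) = 19.9%, a fall of 17%

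With s = 5% and p = 5–15%, m = 1.5–3, the apparent fall lies between 11% and 23%. This shows how untouched older events dilute a change. It does not predict the survey's result, because the survey is a single cross-section.

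**Step 4: reach back before the programme.** The Background dates the programme's introduction to the "President’s Emergency Plan for AIDS Relief (PEPFAR) in 2014", and the survey runs in 2017/2018. A participant aged 24 at the survey was therefore about 20 or 21 in 2014 (24 − 4 or 24 − 3). Open-ended physical items can pick up events from before that age. The article gives no rollout date for the four districts, so the share of such events is unknown.

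**The case against.** The strongest reply is that the deciding source is not at hand. The items belong to a questionnaire and a cited instrument, and a condensed article need not print item stems. The article never says lifetime or ever; it sets a one-year window for the outcome, and the closing time phrase in the item sentence may have been meant for both sets. On that reading nothing is inflated. The case rule also classifies a woman as having experienced IPV without saying that this is the past-year indicator, so a separate restriction might exist.

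Much of this stands. A reader might infer that the survey's past-year prevalence is inflated and does count violence from before DREAMS. The article does not support that as a fact: it shows neither the item stems, nor any IPV figure, nor the district rollout dates. The ratios above show only what would follow from open-ended items.

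It does not remove the point. The time phrase sits only in the clause on sexual violence, the physical clause has its own descriptor, and the two are set against each other. No other section supplies a window for the physical items or limits the case rule. This is a mismatch between what the article states as outcome and what it states as measure, and not merely detail left out.

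It can also be said that IPV is only broken down by DREAMS exposure, with no formal test, and that the Discussion already concedes limited causal inference and no measurement of behavioural change. This is fair, and it keeps the consequence modest. It does not mend the label on the prevalence itself.

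**Conclusion.** The point holds as a mismatch on the face of the text: the outcome is past-year, while five of its eight defining items are described without a one-year limit, and the answers cannot date events. If the description is accurate and the rule feeds the past-year prevalence, the result is at least as high as true past-year IPV. It may also rise with age through accumulated exposure and may include violence older than the programme.

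Only the direction follows from the article. The size does not: the illustrative ratios of 1.16 to 2.66 rest on assumed prevalences, an assumed ratio of ever to past-year physical violence, and independence. With a 12-month window already in the physical items the ratio is exactly 1, and what remains is a wording error. The outcome is secondary, and the primary HIV-incidence analysis is unaffected.

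**What to change.** Check the window in the five physical items, then classify past-year IPV only from items that ask about the previous 12 months.

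- **If the physical items are open-ended:** report ever physical IPV and past-year sexual IPV as two outcomes, and do not label the eight-item composite as past-year.
- **If they already carry a 12-month window:** correct the item description and say that the case rule refers to that period.

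Neither route changes data collection. The cost is two indicators in place of one, or a lower stated IPV prevalence. Rewording the physical items would also give a single window, but it costs more: the article describes the set as already in wide use in South Africa, and its ethics section requires translation and back-translation of the instruments, which would have to be repeated for the changed items.

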Each DREAMS country has identified context relevant interventions to include as part of an evidence-based approach to HIV prevention. In South Africa, DREAMS interventions are rolling out in five high HIV burden districts, namely: City of Johannesburg, Ekurhuleni, eThekwini, uMgungundlovu and uMkhanyakude. The DREAMS initiative is executed through existing U.S. government funded programme implementers including community, faith-based and non-governmental organizations, referred to as implementing partners, along with South African Government structures operating at the provincial, district, sub-district, metro, ward and village level. DREAMS aims to scale-up impactful and evidence-based interventions targeting AGYW, in an effort to bring the HIV/AIDS epidemic under control.

The DREAMS suite of interventions includes condom promotion and provision, HIV Counselling and Testing (HTS) and linkages to care, pre-exposure prophylaxis (PrEP) (targeting sex workers specifically), GBV prevention as well as post-violence care and support; linkage to sexual reproductive health (SRH) services, comprehensive sexuality education and social asset building. DREAMS initiatives aim to strengthen school-based HIV and GBV prevention efforts, together with strengthening community mobilisation and norm change efforts through parenting and caregiver programmes, social protection initiatives and interventions specifically targeting male sex partners. The age range of participating AGYW varies across these different activities. For example, 10–14 year olds are not included in condom promotion activities, while PrEP is provided to young women aged 20–24 years who engage in sex work [31]. Whilst younger girls together with boys and men are targeted by some of the aforementioned interventions, this study focuses on females aged between 12 and 24 years of age. The evaluation will provide data on the impact of the DREAMS interventions and will inform future development and potential expansion of these interventions targeting adolescent girls and young women.

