### Study procedures

#### Recruitment

The study team will establish Community Research Support Groups (CRSG) in all the study districts following the model adopted by the HIV Incidence Provincial Surveillance System (HIPPS) in the uMgungundlovu district [44]. Data collection will be preceded by building strong community relationships through extensive community engagement and advocacy with local stakeholders including traditional leaders, DREAMS implementing partners, other public, private and NGO service providers within the study districts related to education, psycho-social support, socio-economic support as well as health services. The CRSG will provide a forum for the engagement between researchers and community members, preserving the community’s best interests and ensuring that the study team are aware of any concerns about the research. As with HIPSS, the CRSG will provide input into the informed consent procedures, questionnaire design and administration of the surveys [44].

Following community sensitisation, study staff will approach households included in the sample and introduce the study to the household residents. All individuals in the household who meet the eligibility criteria and are available to be interviewed will be asked to participate in the study. Those who do not wish to participate in the study will be asked to provide feedback about their decision for declining in order to characterise the impact of refusal on the study’s outcomes. Those who agree to participate will be asked to designate a location, either inside or outside their residence, where the survey instruments can be administered and biological samples collected privately.

Participants in the study will be compensated nominally for their time with a gift to the value of between 2 and 3 United States Dollars. A Parent/guardian of AGYW aged 12–17 years will be asked to complete a caregiver questionnaire (See addional file 2). No biological samples will be collected from caregivers, defined as a parent or guardian who is primarily responsible for the pre-selected AGYW’s welfare, specifically the person who prepares meals, seeks medical attention for the AGYW in the case of illness and otherwise cares for the AGYW.

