### Analysis of secondary objectives

**Measure HIV prevalence, and proportion on ART and ART naïve with detectable and undetectable HIV-1 viral load**: HIV prevalence will be expressed as the proportion testing HIV positive, where the denominator is all who provided a blood sample for HIV testing and had a conclusive result. The proportion of HIV positive AGYW on ART and those not on ART who have detectable or undetectable viral loads will be determined through laboratory tests that have a dynamic range of 20 to 10 million copies/ml. HIV-1 viral load data and Antiretroviral (ARV) drug measurement data will be used to determine the proportion of HIV infected persons on ART and ART naïve with detectable and undetectable viral loads. Participants who achieve viral suppression will be defined as those with a viral load < 1000 copies/ml. Estimated prevalence will take the survey design and sampling weights into account.

**Measure prevalence of pregnancies and sexually transmitted infections (STIs)**: Pregnancy and STIs (overall and individual diseases: (HBV, HSV-2, Syphilis, HPV, *C.trachomatis, N. gonorrhoea, T. vaginalis* and *M. genitalium*) will be calculated with 95% Confidence Interval (CIs). Pregnancy prevalence is defined as the proportion of AGYW testing positive for pregnancy from their blood samples, where all AGYW tested for pregnancy in this study is the denominator. Individual STI prevalence is calculated as the number of individuals testing positive for a particular STI, divided by all AGYW who were tested for STIs. Secondary analysis will be disaggregated by age, gender, marital status, occupation, employment status and educational attainment as well as other socioeconomic indicators and exposure to DREAMS interventions. All estimates will take the survey design and sampling weights into account.

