**To measure the exposure to the DREAMS programme including condom promotion and provision (male and female); HTS and linkage to care; GBV prevention and post violence care and support; comprehensive sexual reproductive health rights (SRHR) services; social asset building interventions; school-based HIV and violence prevention; community mobilization and changes in social norms; parenting/caregiver programmes:** Composite scores will be created for AGYW and caregivers using self-reported data on their exposure to DREAMS activities. The mean score between AGYW exposed to DREAMS interventions and those who haven’t, will be compared using linear regression and by taking the survey design and sampling weights into account.

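### Post-violence care counts as DREAMS exposure, so splitting intimate partner violence by exposure is biased towards more violence in the exposed, even if DREAMS has no effect

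*Protocol article*

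**What the plan says.** Under Analysis of secondary objectives, the Protocol article describes how exposure to DREAMS will be measured: "Composite scores will be created for AGYW and caregivers using self-reported data on their exposure to DREAMS activities". The activities named there include "HTS and linkage to care; GBV prevention and post violence care and support" and "school-based HIV and violence prevention", together with condom promotion, sexual and reproductive health services, social asset building, community mobilisation and parenting programmes.

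The paragraph on risk behaviour, gender norms, IPV and academic indicators in the same section ends: "Secondary analysis will be disaggregated by age, HIV and STI status and other socio-economic and academic indicators and exposure to DREAMS interventions". The pregnancy and STI paragraph is likewise broken down by "other socioeconomic indicators and exposure to DREAMS interventions". The article gives no other definition of exposure.

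On eligibility, the Background says: "The age range of participating AGYW varies across these different activities". Its example is that "10–14 year olds are not included in condom promotion activities". Under Recruitment: "A Parent/guardian of AGYW aged 12–17 years will be asked to complete a caregiver questionnaire".

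The Discussion says the change in infection rates will be estimated through a population attributable risk. The limitations it lists are the missing comparison arm, limited attribution, and recall and social desirability bias.

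**The concern.** A woman receives post-violence care because she has suffered violence. If that service counts towards exposure, some IPV survivors are classed as exposed, or score higher, because of the outcome itself. Women without IPV have no matching route. The comparison of IPV between exposed and unexposed is then tilted before DREAMS has had any effect.

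The study has no control group, so contrasts by exposure are the main evidence within the study on whether the programme is associated with less violence. A programme that reduces IPV could look ineffective or harmful. Survey weights correct for selection and non-response, not for this. Splitting by age does not remove it either, because it operates within every age group.

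Linkage to care, which follows a positive HIV test, has the same structure. It matters if HIV outcomes are contrasted by exposure, as a population attributable risk would normally require.

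**Working it through.** The plan states no figure on this point, so there is none to reproduce. The check asks what the planned contrast would show if DREAMS had no effect.

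**Inputs (all assumptions; the article gives none of them)**
- b: probability of being exposed through components unrelated to IPV. Main value 30%, range 20% to 60%.
- q: share of otherwise unexposed IPV survivors who receive post-violence care. Range 5% to 30%.
- p: IPV prevalence, 20%. It affects the percentages but not the odds ratio.
- Women without IPV do not receive post-violence care.

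**Any-exposure rule**

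Survivors are exposed with probability b + (1−b)q and unexposed with probability (1−b)(1−q). Other women are exposed with probability b and unexposed with probability 1−b. So

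OR = [(b + (1−b)q) / ((1−b)(1−q))] / [b / (1−b)] = (b + (1−b)q) / (b(1−q)).

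For any q above 0 the numerator exceeds b and the denominator is below b, so the OR is always above 1.

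With b = 30%:
- q = 5%: 0.335 / 0.285 = 1.18
- q = 15%: 0.405 / 0.255 = 1.59
- q = 30%: 0.510 / 0.210 = 2.43

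At q = 15% and p = 20%, IPV in the exposed is 0.2×0.405 / (0.2×0.405 + 0.8×0.3) = 0.081/0.321 = 25.2%. In the unexposed it is 0.2×0.595 / (0.2×0.595 + 0.8×0.7) = 0.119/0.679 = 17.5%.

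Sensitivity to b, for q = 5%, 15%, 30%:
- b = 20%: 0.24/0.19 = 1.26; 0.32/0.17 = 1.88; 0.44/0.14 = 3.14
- b = 60%: 0.62/0.57 = 1.09; 0.66/0.51 = 1.29; 0.72/0.42 = 1.71

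**Multi-item score**

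Assume seven other components, each reaching 30% independently, plus post-violence care as an eighth item. High exposure means a score of three or more. From the binomial distribution (7 items, 0.3), P(3 or more) = 0.3529 and P(exactly 2) = 0.3177. A survivor scores high with probability 0.3529 + 0.3177q; another woman with probability 0.3529 (odds 0.3529/0.6471 = 0.5454).
- q = 5%: 0.3688/0.6312 = 0.5843; OR = 1.07
- q = 15%: 0.4006/0.5994 = 0.6683; OR = 1.23
- q = 30%: 0.4482/0.5518 = 0.8122; OR = 1.49

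**After the fix.** Leaving the item out sets q = 0, and both rules return OR = 1.00 if the remaining components are unrelated to IPV.

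**Age.** The article gives no IPV by age, so female HIV prevalence serves as an age-graded risk: 5.8% at 15–19 and 15.6% at 20–24 (Background), with 3% assumed at 12–14. Take age weights 3:5:5 (equal numbers per year of age), an any-exposure rule, 30% exposed through other components, and no outcome-triggered item.
- Add condom promotion reaching 30% of those aged 15 and over. Unexposed probabilities are 0.70, 0.49, 0.49. Prevalence is 0.5727/6.0 = 9.5% in the exposed and 0.5873/7.0 = 8.4% in the unexposed, ratio 1.14.
- Instead add a school or parenting component reaching 30%, 20% and 2% of the three age groups. Unexposed probabilities are 0.49, 0.56, 0.686. Prevalence is 0.4184/5.3 = 7.9% in the exposed and 0.7416/7.7 = 9.6% in the unexposed, ratio 0.82.

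Unequal eligibility by age therefore distorts the contrast, but the sign depends on which components reach which ages.

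**The case against.** The strongest reply is that the article does not show how exposure is scored. It speaks of composite scores in the plural, gives no items, weights or cut-off, and does not say that a score is the variable used to split IPV. Scores by domain would fit the text, and such detail is often left to the full protocol or analysis plan. Post-violence care also sits beside GBV prevention, which is open to women who have not suffered violence, so many survivors may be exposed anyway. Some recipients will have been hurt by someone other than a partner, or before the past year. They count as non-cases and dilute the bias. The Discussion already concedes limited causal inference, and these are secondary breakdowns.

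Much of this bears on size, and it stands: no magnitude can be derived from the article. It does not remove the direction for IPV while post-violence care counts as exposure and reaches IPV survivors more often than other women. A score for the GBV domain alone would concentrate the problem rather than avoid it. The limitations listed do not include exposure that results from the outcome.

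Three stronger readings are tempting, and the documents do not support them.
- **STI and pregnancy.** A reader might infer that these would also look worse in the exposed. No listed component is shown to be reachable only after an STI or a pregnancy.
- **HIV.** A reader might infer a biased table of HIV prevalence by exposure. No such table is stated outright; only the population attributable risk hints at an HIV contrast by exposure.
- **Age.** A reader might infer that the condom-promotion age limit makes the exposed look worse. School-based and parenting components, and caregiver data for ages 12–17 only, may favour younger girls. Age is also a planned breakdown, which would reduce this part if crossed with exposure.

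**Conclusion.** The concern holds for IPV. On the only definition of exposure in the article, the planned split of past-year IPV by exposure includes a service that follows violence, and under no DREAMS effect it is biased towards higher IPV in the exposed. As an illustration, the spurious odds ratio is 1.18 to 2.43 under an any-exposure rule (30% exposed through other components, 5% to 30% of otherwise unexposed survivors receiving care). It is 1.07 to 1.49 for the eight-item score above. These figures rest on assumed inputs, on the other components being unrelated to IPV, and on women without IPV not receiving the service.

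For HIV the point is conditional: linkage to care causes the same bias if HIV outcomes are contrasted by exposure, including in the population attributable risk. Unequal eligibility makes exposure non-comparable across ages, in a direction the documents do not determine. The primary incidence estimate itself is not affected.

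**What to change.** - For IPV and GBV outcomes, define exposure without post-violence care.
- For any contrast of HIV outcomes by exposure, including a population attributable risk, define exposure without linkage to care.
- Report these two services separately, as coverage among those eligible for them.
- Compare exposed and unexposed within age bands, or score exposure as the share of components open to the participant at her age.
- State in the secondary analysis section which exposure variable is used for each outcome.

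Provided post-violence care and linkage to care are recorded as separate questionnaire items, this is recoding of data the survey already collects, with no new sampling. The cost is that more than one version of exposure must be reported and explained.
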